### Parenting stress assessment: parenting stress index-short form (PSI-SF)

The PSI-SF is a brief and well-validated clinical and research 36-item tool to assess parenting stress [34]. The 5-point Likert response options for each item range from “strongly disagree” to “strongly agree” corresponding to scores from 1 to 5; the higher the score, the greater the levels of parenting stress are. Parenting stress of mothers will be conducted in waves 4–6.

### Socio-demographic and biomedical information of infants

The socio-demographic information of the children will be abstracted from the birth certificate files in wave 1; these will include sex, birth weight, recumbent length, birth date, pregnancy duration, mode of delivery. The data on infant growth will be based on the weight and length measurements that will be conducted by pediatricians when infants visit the study center for vaccination in waves 2–6.

### Cognitive assessment of infants: caregiver reported early childhood development instruments (CREDI)

The CREDI was developed by Harvard University to assess the cognitive development of infants and toddlers aged 0–35 months. The scale is divided into 6-months age intervals and includes 20 questions at each interval [35]. The portion for the scale corresponding to infants aged 0–12 months will be included in this study. Part A of the scale targeting 0–5 months old infants will be conducted in wave 3, part B focusing on aged 6–11 months old infants in wave 4–5, and part C for 12–17 months old infants will be conducted in wave 6. This will allow us to generate prospective data on the evolution of the children’s motor, psycho-social and cognitive development. Since there is a lack of breastfeeding studies in China addressing responsive feeding, we had to use internationally accepted scales to study responsive feeding approaches to breastfeeding (i.e. responsive breastfeeding) and other infant feeding practices among Chinese infants. As far as we know, this will be the first time such scales are used in China.

### Data management and quality assurance

The original data will be stored in the questionnaire system under the principal investigator’s (PI) account and can only be accessed and downloaded by authorized team members of this study. In order to facilitate the management of the research centers ability to tracking participants, the sub-accounts of each center will provide authority only to view the data collected but will not allow for any changes or deletion of data. The questionnaires applied across the 6 waves will be linked using the name and phone number of mothers, their research center and the vaccination schedule of the infants. The PI will carry out data quality control measures, and each research center will receive feedback on their data collection efforts every two weeks. The study’s information system will also help the hospitals track the study’s participants to minimize dropouts. The follow-up tracking system will be implemented by local staff based at each of the five research centers. The participants’ contact information have and will continue to be shared with the PI who will then enter it in the study’s database. All study data will be stored in a password protected Excel file with double backup. We have already learned that the management of the participants in the research center needs to be improved as some have missed some waves of the study. The solution is to follow up with them through the online survey system described in data collection section.

### Current progress and optimization

Recruitment in the five research centers was suspended since January 2020 due to the COVID-19 outbreak when most clinical services were halted, and strong social distancing and isolation measures began to be implemented. The study will restart in 2021. So far, a total of 104 participants have enrolled in the study, 92 completed the wave 1 survey and 12 participants completed the other waves of the study but missed the baseline survey due to missing the short 72-h window of the wave 1 survey. The average age of the recruited mothers is 29.3 ± 4.2 years, the average height is 159.8 ± 5.3 cm, and the average pre-pregnancy weight is 54.4 ± 9.5 kg (Table 2).

**Table 2 Tab2:** Descriptive analysis of the participants in the multi-center longitudinal study on responsive breastfeeding in China as of October 2020 (*N* = 104)

Basic information	mean ± SD / n (%)
Study setting	
Chongqing	57(54.8)
Huizhou	31(29.8)
Guangzhou	16(15.4)
Study wave	
1	92(88.5)
2	26(25.0)
3	16(15.4)
4	7(6.7)
5	0
6	1(1.0)
Age at delivery (y)	29.3 ± 4.2
Pre-pregnancy height (cm)	159.8 ± 5.3
Pre-pregnancy weight (Kg)	54.4 ± 9.5
Marital status (%)	
Yes	90(88.5)
No	2(1.9)
Education (%)	
Primary school or below	0
Middle school	14(13.5)
High school	17(16.3)
University or above	61(58.7)
Monthly income (%)	
≤ 5000	22(21.2)
5001–10,000	42(40.4)
10,001–20,000	22(21.2)
> 20,000	5(4.8)
Unknown	1(1.0)
Current work status (%)	
Working	16(15.4)
Not working	26(25.0)
On maternity leave	50(48.1)
Maternity leave duration	
< 3 months	7(6.7)
4–6 months	48(46.2)
> 7 months	4(3.8)
None	11(10.6)
Works at home	11(10.6)
Not working for 1 year	11(10.6)

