### Data collection

The electronic self-administered questionnaires were developed by team members with strong expertise in maternal-child public health nutrition. All data will be collected via an online questionnaire management system (www.wjx.cn) popular and widely used in China, and that is similar to SurveyMonkey®. We developed the electronic version of all the self-administered questionnaires before recruitment started, pretested and released them for participants to fill in on the study’s secure web-based system. Local doctors who are responsible for recruitment will undertake quality control for the survey and will ensure only the eligible participant could access to the survey system. This approach has been successfully implemented in other studies with similar populations in China [28–30]. The specific procedures followed across the six survey waves are shown in Fig. 2. The first survey (wave 1) will be completed within 72 h after delivery on-site under the supervision of a health care provider. Participants can fill out the questionnaires for the remaining five surveys either on-site or at home by clicking the web link forwarded to them.

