### Socio-demographic data of mothers

Socio-demographics will be collected from wave 1 to wave 6 via the self-administered questionnaires. The information collected in wave 1 will include maternal date of birth, marital status, maternal educational attainment, current employment status, duration of maternity leave, household monthly income, height and weight at beginning of pregnancy, weight gain during pregnancy, pregnancy complications and smoking status during pregnancy. The data on current employment and maternity leave status will be also be collected at waves 2, 3 and 4. The information on date of birth and current employment status will be collected for verification purposes at waves 5 and 6.

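### Education, income and other fixed maternal items are scheduled only for the 72-hour survey, so mothers kept in the cohort without it have no planned source of socioeconomic data

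*Protocol article*

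**What the plan says.** The section Socio-demographic data of mothers opens broadly: "Socio-demographics will be collected from wave 1 to wave 6 via the self-administered questionnaires". Table 1 likewise marks socio-demographic information at all six waves. The section then sets out the content wave by wave.

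- Wave 1 includes "maternal educational attainment, current employment status, duration of maternity leave, household monthly income, height and weight at beginning of pregnancy", together with marital status, gestational weight gain, and "pregnancy complications and smoking status during pregnancy".
- For the middle waves: "The data on current employment and maternity leave status will be also be collected at waves 2, 3 and 4".
- For the last two: "The information on date of birth and current employment status will be collected for verification purposes at waves 5 and 6".

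On how wave 1 is done, Data collection says: "The first survey (wave 1) will be completed within 72 h after delivery on-site under the supervision of a health care provider". It allows completion at home by web link only for the other five surveys.

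The progress section reports that "a total of 104 participants have enrolled in the study, 92 completed the wave 1 survey", and that "12 participants completed the other waves of the study but missed the baseline survey due to missing the short 72-h window". Data management and quality assurance acknowledges missed waves. Its remedy is online follow-up through the system described under Data collection.

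The outcomes and covariates section names socioeconomic status as a covariate. Statistical analysis names it as an effect modifier to be tested, and plans mixed models adjusted for static as well as time-varying covariates.

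**The concern.** Fixed facts such as education and household income are tied to a survey with a very short window, which some mothers have already missed while staying in the cohort. The list of later content does not bring these items back. The study asks whether social determinants create barriers to responsive feeding, so education and income are central to its question. Women who give feeding, growth and development data but have no recorded socioeconomic status cannot contribute fully to that question. The gap comes from where the items sit in the questionnaire, so it can be avoided.

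The same gap shows in the progress table, where the maternal characteristics are described on a base that does not match the women with data.

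**Working it through.** **Step 1. Which items have a later source?** From Socio-demographic data of mothers:

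| Item | Wave 1 | Waves 2–4 | Waves 5–6 |
|---|---|---|---|
| Education, income, marital status | yes | not listed | not listed |
| Pre-pregnancy height and weight, weight gain | yes | not listed | not listed |
| Pregnancy complications, smoking | yes | not listed | not listed |
| Employment | yes | yes | yes (verification) |
| Maternity leave | yes | yes | not listed |
| Date of birth | yes | not listed | yes (verification) |

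Table 1 has a single row for all socio-demographic content, so it does not show which items recur.

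**Step 2. Does the follow-up remedy reach wave 1?** Data management refers back to Data collection. That section offers the home web link for the five later surveys and keeps wave 1 on site within 72 hours. As written, the remedy does not extend to the wave 1 items.

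**Step 3. Size so far.** 92 + 12 = 104, as stated. The proportion without wave 1 is 12/104 = 11.5%; the exact (Clopper–Pearson) 95% interval is 6.1% to 19.3%.

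Table 2 shows 26, 16, 7, 0 and 1 records at waves 2 to 6, a total of 50. Between 26 women (all later records belong to women seen at wave 2) and 50 women (no overlap) therefore have any follow-up. The 12 are between 12/50 = 24% and 12/26 = 46% of them.

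**Step 4. Projection, assuming that the rate persists.** 700 × 12/104 = 80.8, about 81 women. Over the interval: 700 × 0.061 = 43 to 700 × 0.193 = 135.

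**Step 5. Scale against the design.** First the protocol's own figure, with p₁ = 0.36, p₂ = 0.23, mean 0.295, two-sided 5% and 90% power:

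- √(2 × 0.295 × 0.705) = 0.6449
- √(0.36 × 0.64 + 0.23 × 0.77) = 0.6384
- n = (1.960 × 0.6449 + 1.2816 × 0.6384)² / 0.13² = 256.5, so 257 per group and 514 in all. This agrees.
- 514/0.75 = 685.3, so 686; the target of 700 covers it.

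After 25% loss, 700 × 0.75 = 525 remain. If a further 11.5% were excluded without overlap, 525 × 92/104 = 464 would remain. Power is Φ[(0.13√n − 1.960 × 0.6449)/0.6384], with n per group:

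- n = 262.5: Φ(1.319) = 90.6%
- n = 232.2: Φ(1.123) = 86.9%

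This only gives a sense of scale, because the design comparison is of crude urban and rural rates.

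**Step 6. Table 2.** Category sums:

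- marital status: 90 + 2 = 92
- education: 14 + 17 + 61 = 92
- income: 22 + 42 + 22 + 5 + 1 = 92
- work: 16 + 26 + 50 = 92
- leave: 7 + 48 + 4 + 11 + 11 + 11 = 92

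The percentages for education, income, work and leave use 104. University education is printed as 58.7% (61/104); among women with data it is 61/92 = 66.3%. Married is printed as 88.5%, but 90/104 = 86.5% and 90/92 = 97.8%. The printed value equals 92/104. The setting rows (57 + 31 + 16 = 104) and the wave rows correctly use 104.

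**The case against.** The case on the other side limits the point in several ways.

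- **These items are never supplied.** A reader might infer this, but the article does not say so. Socio-demographics are marked at every wave, online follow-up exists for missed waves, and a full protocol may hold item-level branching. What stands is that no passage states that the wave 1 items are asked later, and that the passages do not agree with each other.
- **These mothers drop out of every adjusted model.** This would require complete-case analysis and a wave-1-only variable in every model. The article states neither, and missing-data handling may lie in an analysis plan that is not shown. Models adjusted only for location, centre, employment or leave could keep these women. Smoking and pre-pregnancy size are collected but are not individually named as covariates.
- **Table 2 proves that the 12 gave none of these data.** It does not. Employment and leave also stop at 92 although both are asked again at waves 2 to 4. The table may simply tabulate wave 1 records.
- **They joined later than the others, so breastfeeding-duration analyses need delayed entry.** The article says only that they missed the baseline survey. Screening takes place within 72 hours of delivery, so enrolment followed by a missed questionnaire is equally possible. No time-to-event analysis is described, and duration is listed as an independent variable.
- **Size.** The rate comes from 104 women in a phase cut short by the pandemic. Closer supervision has since been arranged, and women who miss wave 1 may overlap with those lost later. The crude urban–rural comparison behind the sample size needs neither education nor income.

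These limits narrow the consequences. They do not supply a source for the items. If an unseen plan provides for imputation, it would still be a poor substitute for asking a mother her education.

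**Conclusion.** The point holds in a limited form. As scheduled, mothers who miss wave 1 but remain in the cohort have no planned source for education, income, marital status, pre-pregnancy size, pregnancy complications or smoking. Socioeconomic status is the part that matters most, since the plan names it as both covariate and effect modifier.

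The observed size is 12 of 104. The figure of about 81 of 700 (range 43 to 135) rests on that rate persisting. Exclusion of these women rests on complete-case analysis in models that use the wave-1-only items. The power figures further assume no overlap with the 25% attrition, and they suggest a moderate loss. The article does not break the 12 down by centre, so it cannot be said whether the gap falls unevenly between urban and rural mothers.

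The Table 2 base and the marital-status entry are real but secondary reporting errors. They do not affect the planned design.

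**What to change.** 1. In Socio-demographic data of mothers, attach the fixed socio-demographic and pregnancy block to the first survey each mother completes, whichever wave that is.
2. Collect the block from the existing 12 mothers at their next web contact.
3. Reconcile Data collection, Table 1, Socio-demographic data of mothers, and Data management and quality assurance, so that they agree on which items are asked when and how a missed wave 1 is made good.
4. In Table 2, base the maternal percentages on the 92 women with data, or keep 104 and add a missing row. Correct the marital-status entry to match the chosen base.

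The cost is one branch in the online questionnaire and a few extra minutes for the mothers concerned. A few items, such as pre-pregnancy weight, would be recalled somewhat later than 72 hours; education is hardly affected by the delay.

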### Statistical analysis

Descriptive analysis will be performed to describe the socio-demographic characteristic of the participants and to summarize the scale scores of the questionnaires. In order to identify the inequity factors of RF, the crude and adjusted breastfeeding rates for urban or rural residence and the associations between RF and early childhood development outcomes will be estimated with their corresponding 95% confidence intervals (95% CI). Continuous variables will be presented as mean with standard deviation (SD) or median with interquartile range (IQR). After testing for the normality of the distribution means will be compared using Student’s t test or analysis of variance. Categorical variables will be presented as counts with percentages and compared using Person’s χ^2^ test or Wilcoxon rank-sum test between groups, such as urban and rural.

For the cross-sectional analysis of the data, logistic regression and linear regression will be performed to identify barriers and facilitators of RF or infant growth and development, respectively. Interactions among the latent influencing factors will be performed using multivariable analysis to test for potential effect modification taking inequities indicators into account, such as socioeconomic status, psycho-emotional status and maternal health care access. For the longitudinal data analysis, linear mixed effect model or multilevel mixed-effects models will be performed to determine the association between RF and infant growth and development after adjusting for time dependent and static covariates. The statistical significance will be considered as a two-tailed *p* value ≤0.05. All data will be analyzed using Statistical Analysis System (SAS Institute Inc., Cary, North Carolina, USA).

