### Sample size calculation

From the perspective of health equity, we designed the study to enroll participants from rural and urban areas. We estimate the sudy sample size based on the different prevalences of breastfeeding in urban an rural areas.

The sample size was calculated using the following formula for comparison of two proportions:
$$ {\mathrm{n}}_{\mathrm{urban}}={\mathrm{n}}_{\mathrm{rural}}=\frac{{\left[{\mathrm{Z}}_{1-\upalpha /2}\sqrt{2\overline{\mathrm{p}}\left(1-\overline{\mathrm{p}}\right)}+{\mathrm{Z}}_{\upbeta}\sqrt{{\mathrm{p}}_1\left(1-{\mathrm{p}}_1\right)+{\mathrm{p}}_2\left(1-{\mathrm{p}}_2\right)}\right]}^2}{{\left({\mathrm{p}}_1-{\mathrm{p}}_2\right)}^2} $$where *n*_urban_ and *n*_rural_ are the sample sizes corresponding to the urban and rural groups, respectively; *Z*_*1-α/2*_ and *Z*_*β*_ are the Z values corresponding to the alpha (*α*) and beta (*β*) error, respectively; *p*_1_ and *p*_2_ are the estimated proportion of breastfeeding rates in urban and rural areas, respectively, while $$ \overline{p} $$ is the average of *p*_1_ and *p*_2_.

According to the China Development Research Foundation (CDRF) 2019 *Report on National Survey of Factors Influencing Breastfeeding*, the prevalence of breastfeeding during the first six months of life in large cities (estimated *p*_1_) and medium/small cities (estimated *p*_2_) was 36 and 23%, respectively. With a statistical power of 90% and a two-tailed significance level of 5%, we estimated that a minimum of 257 participants for each group (urban and rural), should be recruited respectively. Therefore, a sample of 514 are required to observe a 13% difference in the prevalence of breastfeeding between the two groups. Taking into consideration that 25% participants may be lost to follow-up, our goal is to enroll 700 participants.

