According to our current research progress, we find that the the ability to recruit and follow-up partcipants varies across centers. This difference may be related to the economic, cultural, and urban-rural discrepancy and may also reflect health inequities in access to breastfeeding support. For example, the center in the large city of Chongqing has been more successful with recruitement and retention than the two rural centers in Huizhou. In order to increase participation and obtain more accurate data on breastfeeding barriers and facilitating factors, we have arrange for dedicated medical staff to supervise more clcosely the study’s staff at the centers. The PI will provide coitnuous feedback to each center based on the completeness and quality of participant’s questionnaire responses.

We acknowledge that a potential limitation of this study is that the five selected research centers do not represent all the regional variation of health care facilities across China. An additional limitation is that the CREDI has not been previously validated in China. As in any prospective study, attrition is likely to happen. In the context of China, the most likely reason is for moving to other place in search of jobs. In order to minimize attrition, we designed the study data collection points aligned with the compulsory vaccinations schedule for mothers to remember when they need to fill out their surveys and they will be rceiving reminders before their survey date. Furthermore the doctor seeing the mothers, who is a very influential figure in Chinese culture, will strongyl encourage them to fill out the survey. Lastly, if they do not complete the survey as scheduled they will be sent up to 3 reminders to do so. Despite these limitations, we believe that this study will inform evidence-based policies in China to promote breastfeeding and advocate responsive feeding from the repsonsive parenting perspective taking health equity and the social determinants of health into account. This approach is needed to further promote the healthy growth and development of Chinese infants.

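### The rule for comparing means tests normality but then uses equal-variance tests, which could miss 5% if enrolment stays unequal; Welch's versions avoid this at almost no cost

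*Protocol article*

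**What the plan says.** The Statistical analysis section of the protocol article sets the rule for continuous variables: "After testing for the normality of the distribution means will be compared using" Student's t test or analysis of variance. Medians with IQRs are allowed as descriptive summaries, but no test is attached to them. The rank-sum test appears only in the next sentence, on categorical variables: Pearson's chi-squared "or Wilcoxon rank-sum test between groups, such as urban and rural". No equal-variance condition and no unequal-variance version is named. Significance is judged two-sided at 0.05.

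Three other places bear on this:

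- The Abstract (Methods) says urban and rural participants will be compared on the psychological, feeding, growth and development measures at every time point. Unadjusted comparisons of means are therefore a stated use of the rule.
- The Sample size calculation plans equal groups: "a minimum of 257 participants for each group (urban and rural), should be recruited respectively".
- Table 2 gives enrolment by city (Chongqing 57, Huizhou 31, Guangzhou 16, total 104), and the Discussion reports that "the center in the large city of Chongqing has been more successful with recruitement and retention than the two rural centers in Huizhou".

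**The concern.** The rule checks an assumption that hardly matters here and is silent on the one that can. With some 250 or more mothers per group, the sampling distribution of a mean is close to normal even for a skewed, bounded score such as the EPDS (0 to 30). A normality test at that size can nevertheless be expected to reject for such scores. The stated rule then gives no way forward, because the only rank test is attached to categorical data.

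Student's t test and classical ANOVA pool the variance across groups. With equal group sizes that is harmless for the two-group test. With unequal sizes it is not. If the smaller group is the more variable, the standard error is too small, so P values are too small and intervals too narrow. If the smaller group is the less variable, the reverse holds. At stake are the unadjusted urban-rural and between-city contrasts in the EPDS, ERQ, PSI-SF, IFSQ and CREDI scores, weight and length.

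**Working it through.** **1. The plan's own figure.** Inputs from the Sample size calculation: rates of 0.36 and 0.23, 90% power, two-sided 5%, equal groups. The mean rate is 0.295.

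- First term: 1.960 × √(2 × 0.295 × 0.705) = 1.960 × 0.6449 = 1.2641
- Second term: 1.2816 × √(0.36 × 0.64 + 0.23 × 0.77) = 1.2816 × 0.6384 = 0.8181
- n = (1.2641 + 0.8181)² / 0.13² = 4.335 / 0.0169 = 256.5, so 257 per group. This matches the plan.
- 514 / 0.75 = 685.3, so 686, rounded up to 700. Expected completers: 700 × 0.75 = 525.

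**2. The split so far.** Study setting lists centers one (Chongqing) and two (Guangzhou) as urban, three as mixed, and four and five as rural. Centers three to five make up Huizhou. From Table 2, 57 + 16 = 73 of 104 (70.2%) come from urban centers and 31 of 104 (29.8%) from Huizhou. If the two urban centers enroll only urban residents, at most 31 are rural.

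**3. Error rate of Student's t.** For urban n1 with SD 1 and rural n2 with SD r:

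- true variance of the difference: Vt = 1/n1 + r²/n2
- variance the pooled test uses: Vp = [((n1 − 1) + (n2 − 1) r²) / (n1 + n2 − 2)] × (1/n1 + 1/n2)
- true two-sided error ≈ 2[1 − Φ(1.96 √(Vp/Vt))]

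With n1 = n2 = n, both variances equal (1 + r²)/n. The ratio is 1 and the error stays at 5% whatever r is.

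Assumed case: the 70:30 split carried to 525 completers (368 and 157).

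- r = 1.5: Vt = 0.01705; Vp = 1.3728 × 0.009087 = 0.01247; √(Vp/Vt) = 0.855; error = 2[1 − Φ(1.677)] = 9.4%. Intervals are about 14% too narrow.
- r = 0.67: Vt = 0.005577; Vp = 0.8356 × 0.009087 = 0.007593; √(Vp/Vt) = 1.167; error = 2[1 − Φ(2.287)] = 2.2%. Intervals are about 17% too wide.

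**4. Simulation check.** Normal data, 100,000 runs per cell, true size at nominal 5%:

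| Split | SD ratio 0.67 | 0.8 | 1.0 | 1.25 | 1.5 |
|---|---|---|---|---|---|
| 257:257 (planned) | 5.1% | 5.0% | 4.9% | 5.0% | 4.9% |
| 73:31 (now) | 2.3% | 3.3% | 5.0% | 7.4% | 9.3% |
| 70:30 of 525 | 2.2% | 3.3% | 5.1% | 7.3% | 9.4% |
| 80:20 of 525 | 1.4% | 2.5% | 4.9% | 8.5% | 12.2% |

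The error depends on the split and the SD ratio, and hardly on the total. Welch's test stayed between 4.9% and 5.2% in every cell.

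**5. Price of Welch's test when the variances are equal.** 400,000 runs, differences set for about 90% and 80% power:

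| Split | Student, then Welch (90%) | Loss | Student, then Welch (80%) | Loss |
|---|---|---|---|---|
| 257:257 | 89.96%, 89.96% | 0.0 | 79.80%, 79.80% | 0.0 |
| 70:30 of 700 | 89.84%, 89.77% | 0.1 | 79.90%, 79.79% | 0.1 |
| 70:30 of 525 | 89.86%, 89.77% | 0.1 | 79.80%, 79.66% | 0.1 |
| 73:31 | 89.38%, 88.93% | 0.5 | 79.22%, 78.57% | 0.7 |

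The same mechanism applies to ANOVA across cities (57/31/16), groups for which the plan sets no equal sizes. No error rate was calculated for that case.

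**The case against.** The strongest reply is that the harm needs two conditions that the documents do not establish. First, the plan is for equal urban and rural groups, and there Student's t is exact enough at any SD ratio. The 73:31 split is interim, at 104 of 700, and the Discussion describes closer supervision and feedback to the centers to raise participation. Second, no SD is given by area. Table 2 has overall SDs only, so the ratios used here are assumptions, and at 1.0 nothing goes wrong. Both points stand, and they make the finding conditional.

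Huizhou is also not a purely rural group, so 70:30 is only a stand-in for the urban-rural split by residence. That stands too, although counting some Huizhou women as urban would make the split more uneven, not less. It is fair to add that the normality argument uses the planned size while the imbalance uses current enrolment. At 31 women the claim that non-normality matters little is weaker. The error rates, however, are nearly the same at 73:31 and at 70:30 of 525, so they do not depend on mixing the two.

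The article is condensed, and an analysis plan that is not shown may settle the fallback for scores that fail the check; the placement of the rank-sum test may be compressed wording. But the article does name Student's t test, so a different default would depart from the printed rule.

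A reader might infer that the study's error rate will be wrong, that the urban-heavy split is part of the design, or that the regressions need robust standard errors. The documents support none of these. The main growth and development analyses are linear regression and mixed models, and no defect is shown there.

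**Conclusion.** The point holds as a minor, conditional one. The rule lets a normality test lead to equal-variance tests and names nothing for continuous scores that fail it. If urban and rural numbers end equal, Student's t keeps 5% for that contrast. If a split near 70:30 persists, and the rural/urban SD ratio lies between 0.67 and 1.5, the true error rate of a nominal 5% test could be about 2% to 9%. The direction depends on which group varies more, and at a ratio of 1.0 there is no error. The persistence of the split and the SD ratios are assumptions. The effect is confined to unadjusted comparisons of means; the regressions, the mixed models and the two-proportion sample size are untouched. Since the final group sizes and SDs are unknown, and the Discussion reports better recruitment and retention in Chongqing than in the rural centers, a default that is valid in either case is the better choice.

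**What to change.** Replace the sentence in Statistical analysis with one saying that unadjusted comparisons of continuous scores use Welch's t test (two groups) or Welch's ANOVA (three or more), whatever a normality test shows, and that mean differences are reported with 95% CIs. Distribution checks can stay for choosing between mean with SD and median with IQR as the descriptive summary. The rank-sum test can stay for ordered categories. The regression and mixed-model text needs no change on this account.

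The cost is one sentence, made while most participants are still to be enrolled. If the variances are in fact equal, the power loss is nil at 1:1, about 0.1 points at 70:30 of the planned size, and up to about 0.7 points at the current 73:31.
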